### Power calculation

We calculated power on an expected transition rate of 35 percent over eighteen months with a 50 percent reduction of transitions in the CBT-group. The sample we need for a 2-tailed test of the proportions with an alpha of .05 and a power of .80 is 2 × 93 for the reduction of the transition to psychosis and 2 × 82 for the persistence of ARMS and 2 × 91 for the transition into psychosis. A conservative estimate of the drop-out rate is twenty percent per year in schizophrenia research [24]. With an estimated 30 percent drop-out over 18 months, we decided to include 240 persons in the trial. Interventions to minimize drop-outs are flexibility to location of therapy (the appointment can be at their home-address or some times by telephone or webcam), sending Christmas- and Birthday cards every year. For the participants that end up in the CBT-treatment group there is also the possibility for web-cam therapy. All the participants that complete the study will have a financial compensation for expenses made.

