## Background

In recent decades, the number of studies on early detection and intervention in psychosis has increased exponentially. In the UK [1,2], Australia [3], Norway [4] and the Netherlands [5], specialized programs have been developed for first psychotic episode patients. An unexpected finding in a seminal study was the identification of a group of help-seeking young people with sub threshold psychotic symptoms that made a transition to psychosis [6]. This phase prior to a first episode of psychosis, retrospectively called the prodromal period, begins with the first changes in behaviour and lasts until the onset of the first psychotic episode [7]. The prodromal period can be characterized by various mental state features, including non-specific symptoms such as depressed mood and anxiety, negative signs and symptoms as well as sub-threshold or attenuated psychotic symptoms [6]. However, the term "prodromal" is not always correct in prospective investigations. After all, only in the at risk people who actually develop a full-blown psychosis, the symptoms can be defined as 'prodromal'. The majority of individuals who share the same sub-clinical symptoms will recover spontaneously or have persistent sub-clinical symptoms [8] without a transition into psychosis. Instead of putatively prodromal, in prospective studies the subjects are referred to as being at ultra high risk (UHR) or having an At Risk Mental State (ARMS) of developing psychosis.

Yung and McGorry were the first to develop operational criteria to detect people at ultra high risk of developing psychosis, resulting in the Comprehensive Assessment of At Risk Mental State (CAARMS) scale [8]. At first about 40% of the people with ARMS made a transition to psychosis within a year [8,9]. However, more recent studies find lower transition rates (declining to only 16% transition to psychosis at 24 months) [10,11].

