## Discussion

Nowadays, research increasingly focuses on early detection of patients with an At Risk Mental State. The objective is to delay the onset of psychosis or possibly even prevent a psychotic episode. A better understanding of the pre-psychotic phase is necessary to optimise preventive interventions. This study is a pilot for the implementation of early detection and intervention teams in the Netherlands and is of interest for the general mental health field, because indicated prevention for this target population is not available. The study design has a number of important strengths and limitations, as described below.

The evidence for CBT in the prevention of psychosis is still inconclusive. Only one previous study by Morrison and French [14] assessed the use of CBT in people with an ARMS. All the other studies, compared the control group with either a medication group or a combined medication and CBT group [3,12,14,15]. The present study has much more power than the above-cited study to examine the efficacy of CBT in the prevention of psychosis. Our aim is to test an intervention that aims to delay or to prevent the transition into psychosis and to reduce the persistence of ARMS. The study compares treatment as usual (TAU) with TAU plus a manualised CBT. It is partly a twin study of another large trial in the United Kingdom. A number of outcome measures are identical in both cases and we can pool the data afterwards to increase power even more. An important strength in this study is its power to generate conclusive answers on the possibility of prevention in psychosis.

There is a growing concern regarding the use of antipsychotic medication when patients potentially may not need them. Current international guidelines do not support antipsychotic medication in the prevention of psychosis. Medication can have serious side-effects and it is not yet known how long medication should be prescribed in preventing psychosis [49]. Treating people at risk with exclusively psychological means (CBT + education) could be a valuable and more benign alternative to pharmacotherapy. By providing an explanation for their odd experiences people can come to terms with these experiences. If CBT is effective in ARMS, then important goals in mental health care can be accomplished. The use of a benign time-limited intervention in the early stages will be well tolerated, while antipsychotic medication is not very well tolerated because of side-effects.

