A possible strength is the two-stage screening procedure used to detect subjects at risk. Screening the entire help-seeking population referred to community mental health services with a two-stage strategy, can potentially detect more ARMS patients by uncovering at risk cases that would normally never be referred. Many pre-psychotic symptoms are not recognised during the regular referral process. Because we do not want to miss any patients, we probably will not only detect late prodromal patients, but also early prodromal patients. Therefore, this two-stage screening method will detect more ARMS patients than the existing referrals to the specialized clinic, but probably at the expense of more false positives. The referred patients are more likely to be late prodromal than the people recruited by screening. Screening with a highly specific screening tool eliminates most of those not at risk in the first stage. The selected percentage undergoes the second stage of screening with the CAARMS interview. In this enriched sample of (more) psychosis-prone individuals the assessment instruments will probably have a better predictive value. In concordance with previous research [50] we expect about 3.5% of the help-seeking population will have psychotic-like experiences and will have an at-risk mental state. In the selected group we expect the transition rate to be 25 to 35 percent over an 18 month period. If this two-stage screening process proves to be successful, this type of screening could be implemented in routine mental health care.

Another strength of our study is that it has a strong external and internal validity. Since this trial is implemented in a mental health setting, the results will immediately be relevant for clinical practice. All participants receive treatment in a regular outpatient treatment centre in the same way they would have received treatment if they were not enrolled in the study. The internal validity is fine-tuned by supervision of the therapists every two weeks. The researchers and research assistants have supervision every three months. The internal validity is measured by the inter-rater reliability of the CAARMS; the therapy is monitored regularly and reliable and valid instruments are used.

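### Power is calculated only at 35%, the upper bound of the 25 to 35% transition rate the article itself expects, so the stated 80% is not delivered across that range

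*Protocol article*

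**What the plan says.** The Power calculation section of the protocol article states: "We calculated power on an expected transition rate of 35 percent over eighteen months with a 50 percent reduction of transitions in the CBT-group". The test is a "2-tailed test of the proportions with an alpha of .05 and a power of .80", and the resulting size is "2 × 93 for the reduction of the transition to psychosis". The section allows for 30% drop-out over 18 months and sets enrolment at 240.

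The Discussion, at the end of its paragraph on two-stage screening, gives the expectation as a range: "In the selected group we expect the transition rate to be 25 to 35 percent over an 18 month period". Elsewhere the Discussion presents power as a main asset of the trial: "An important strength in this study is its power to generate conclusive answers on the possibility of prevention in psychosis".

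The article gives no power figure for any rate other than 35%.

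**The concern.** Both statements concern transition to psychosis over 18 months. One gives a single value of 35%; the other gives a range whose upper limit is 35%. For a fixed relative reduction, a lower control rate means a smaller absolute difference and lower power, so 35% is the most favourable value the article's own expectation allows.

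At stake is how much weight the stated 80% can bear. If the control rate falls in the lower part of the expected range, the trial has a substantial chance of missing a true halving of transitions, while the text tells readers that its power is a reason to trust its answer.

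**Working it through.** **Inputs**
- Control rate p1: 35% (Power calculation); 25 to 35% (Discussion).
- Effect: 50% relative reduction, so p2 = p1/2 (Power calculation).
- Two-sided alpha 0.05, z = 1.960; power 0.80, z = 0.842 (Power calculation).
- Numbers per arm: 93, the stated requirement; 240/2 = 120, enrolled; 120 × 0.70 = 84, after the stated drop-out. Equal allocation is implied by the 2 × 93.
- Test: unadjusted chi-square (Analyses).

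**Formulas** (pooled two-proportion test, p̄ = (p1 + p2)/2)
- A = √[2p̄(1 − p̄)]; B = √[p1(1 − p1) + p2(1 − p2)]
- n per arm = [1.960·A + 0.842·B]² / (p1 − p2)²
- Power = Φ{[(p1 − p2)√n − 1.960·A] / B}

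**The article's own figure.** With 35% against 17% (half of 35%, rounded down), the formula gives 93 per arm, which is the stated number. With the unrounded 17.5%, A = 0.6222 and B = 0.6098, so n = (1.2196 + 0.5132)²/0.175² = 3.003/0.030625 = 98.0. The 2 × 93 is therefore reproduced, but only with the rounded CBT-arm rate. Against an exact halving, 93 per arm falls slightly short of 80% even at 35%.

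**At 25% against 12.5%.** A = 0.5520 and B = 0.5449.
- 84 per arm: (0.125 × 9.165 − 1.0819)/0.5449 = 0.117, power 0.55
- 93 per arm: (0.125 × 9.644 − 1.0819)/0.5449 = 0.227, power 0.59
- 120 per arm: (0.125 × 10.954 − 1.0819)/0.5449 = 0.528, power 0.70
- For 80% power: n = (1.0819 + 0.4586)²/0.125² = 151.9, that is 152 per arm

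**Across the article's range**

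| Control vs CBT rate | 84 per arm | 93 per arm | 120 per arm | n per arm for 80% (before rounding up) |
|---|---|---|---|---|
| 35% vs 17.5% | 0.74 | 0.78 | 0.87 | 98.0 |
| 30% vs 15% | 0.65 | 0.69 | 0.80 | 120.5 |
| 25% vs 12.5% | 0.55 | 0.59 | 0.70 | 151.9 |

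Exact power of the uncorrected chi-square test agrees closely. At 25% it is 0.557, 0.595 and 0.712 for 84, 93 and 120 per arm; at 35% it is 0.743, 0.787 and 0.877.

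The control rate needed for 80% power is about 39% with 84 per arm, 36% with 93 and 30% with 120.

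**The case against.** **Planning on one value is ordinary, and 35% lies within the stated range.** This is true, and the calculation contains no wrong sum on this point, since 2 × 93 can be reproduced. A condensed article may also leave a table of power over several rates to a fuller document. What stands against this is that the two expectations are both printed here, they differ, and the sample size uses the favourable end without comment.

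**The two rates may not describe the same people.** The Discussion's range closes a paragraph on screening, whereas the trial also enrols Amsterdam clinic referrals, whom that paragraph describes as more likely to be late prodromal. The overall rate could therefore lie towards the upper end. Nor does the text say that the range is a control-arm rate: 35% and 17.5% average about 26%, which is also inside it. The text settles neither question, so the control-arm reading has to be stated as an assumption.

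**The 84 per arm is a floor.** Analysis is by intention to treat with imputation, survival analyses are planned, and transition is checked at months 2, 4, 6, 9, 12, 15 and 18. Participants who leave late still contribute information. This stands, and it is why the 120 column is shown. With no loss, power is about 80% or more from 30% to 35%, and the shortfall is confined to the lower half of the range. It does not disappear: power at 25% is still 0.70.

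**Three stronger readings are not supported.**
- A reader might carry the Background's "declining to only 16% transition to psychosis at 24 months" into the calculation and find still lower power. That figure comes from other studies, at a longer horizon, and lies outside the range this article expects.
- A reader might infer that a non-significant result would be reported as conclusive. The Discussion's sentence describes a strength of the design; it is not a rule for interpreting results, and the same paragraph foresees pooling with a UK trial to increase power.
- A reader might infer that 80% is met at 35% and nowhere else. On the figures above it is not quite met at 35% with 84 or 93 per arm, and it is met down to about 30% with all 120.

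**Conclusion.** The point holds as a mismatch between the planning rate and the stated expectation, with a measurable effect on power. The trial is powered at the upper bound of its own 25 to 35% range, and the stated 80% is not delivered across that range. At 25%, power for a true halving is 0.55 to 0.70 depending on how much information is lost, so a real effect of the planned size would be missed in 30% to 45% of such trials. At 30% power is 0.65 to 0.80, and at 35% it is 0.74 to 0.87.

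These figures assume a 50% relative reduction at every control rate, equal allocation, a two-sided 5% test without continuity correction, and that 25 to 35% is the control-arm rate for all recruitment routes combined. If the range described something else, such as both arms together, the shortfall would have to be recalculated. The need to say which is meant would remain.

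**What to change.** 1. Reconcile the Power calculation section with the Discussion on one expected 18-month control-arm range, saying that it is the control rate and whether it covers both the screened and the clinic-referred participants.
2. Restate power at 25%, 30% and 35% for both the evaluable number (84 per arm on the stated drop-out) and the enrolled number (120 per arm). The table above can serve if the range is kept.
3. Qualify the Discussion's claim about conclusive answers so that it reflects the power at the lower rates.

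The cost is a few sentences and a small table, and a less favourable power statement. Enrolment does not change.

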### Intervention

Participants in the control condition will receive treatment as usual (TAU) for the mental problems that they are seeking help for (e.g., depression, ADHD or anxiety disorder). The subjects in the intervention group will receive TAU plus a manualised cognitive behavioural therapy (CBT). The intervention protocol, based on the protocol from the British intervention trial [20,21], is a cognitive behavioural intervention that aims to reduce symptoms, normalises psychosis-like experiences and prevents a catastrophic appraisal of the psychotic-like symptoms from occurring. The idea is that the final common pathway from ARMS to psychosis is largely based on catastrophising the psychotic-like symptoms which are then worsened by a high level of emotional arousal. When the appraisals become fixed and frightening, delusions are formed. The therapy manual in this study is enriched with eight sessions of psycho-education and behavioural experiments with cognitive biases that play a role in the development of delusions and hallucinations. Normalising the odd experiences as a result of perceptual and reasoning biases is supposed to reduce the emotional arousal and over-involvement with the experiences. Catastrophic delusional interpretation of the unsettling experiences is then probably prevented. Behavioural experiments and homework exercises teach people to tolerate psychosis-like experiences and reduce emotional discomfort. The intervention consists of a maximum of 25 sessions within a six-month period. All therapists are psychologists or consultant psychiatrists experienced in CBT with psychotic patients. They are trained in using the protocol and are offered supervision every two weeks during the course of the trial. During the two-hour supervised sessions, audio-taped sessions are discussed and rated on the Cognitive Therapist Scale [25]. Another part of the supervised sessions is dedicated to case formulation and trouble shooting of difficult cases.

### Measurements

(See also table 4 for measurement moments and instruments)

**Table 4 T4:** measurements

Measurements	T0: baseline	T6: end of the intervention	T12: Follow up	T18: follow up	Transition
CAARMS	X	X	X	X	x

BDI	X	X	X	X	-

SIAS	X	X	X	X	-

EQ5D	x	X	X	X	-

PBIQ-R	x	X	X	X	-

MANSA	x	X	X	X	-

CDS	x			X	x

Verbal Fluency	x	X	X	X	-

Medication check	x	X	X	X	x

Blood sample	x	-	-	-	-

SCAN interview	x	-	-	-	x

PANSS	-	-	-	-	x

PSYRATS	-	-	-	-	x

Treatment check	-	-	-	-	x

CAARMS = Comprehensive Assessment of At Risk Mental State; BDI = Beck Depression Inventory; SIAS = Social Interaction Anxiety Scale; EQ5D = Euroqol-5D; PBIQ-R = Personal Beliefs about Illness Questionnaire-Revised; MANSA = Manchester Short Assessment of Quality of Life; CDS = The Calgary Depression Scale; SCAN = Schedules for Clinical Assessment in Neuropsychiatry; PANSS = Positive and Negative Syndrome Scale; PSYRATS = Psychotic Symptom Rating Scales.

Subjects participate in the study for 18 months. At baseline and at six-month intervals, participants are assessed with the full CAARMS [8]. During these major measurement sessions, participants are also assessed with secondary outcome measures and mediators and moderators. In between the major assessments participants are monitored with a subset of the CAARMS (the first four scales) to assess a possible transition to psychosis. The minor assessments are scheduled at months 2, 4, 9 and 15.

### Instruments

The following instruments are used:

1. The Prodromal Questionnaire (authorized Dutch translation by [name], [name], [name]) [22] will be used to screen patients for psychosis-proneness in the general help-seeking population and is a 92-item self-reporting lifetime questionnaire, rated on a two point scale ('agree' and 'disagree'.) Of these items, 45 apply in the case of possible sub-clinical positive symptoms. When maximizing the true positive cases, Loewy et al. found a cut-off score of eight symptoms at the positive subscale predictive for an ARMS on the SIPS (a CAARMS look-alike) with a sensitivity of 90% and a specificity of 48% in a population that was referred because of suspected prodromal state [22]. Since we expect more false positives in the general help-seeking population, the cut-off score for the EDIE-screening is higher [26]. Patients are invited for a further structured clinical interview when the total score of positive symptoms exceeds 18.

2. The Comprehensive Assessment of At Risk Mental State (CAARMS [8], authorised Dutch version by [name], [name], [name], [name], [name]) [8] is a semi-structured interview that assesses sub-clinical psychotic symptoms in the last year before assessment. Both intensity and frequency of the symptoms are assessed, in order to dimensionally distinguish between not at risk, ARMS and psychosis (see table 1, 2, 3). The CAARMS has a good reliability. High scores on the CAARMS are predictive for transition into psychosis with a relative risk of 12.44 (95% CI = 1.5 - 103.41, *p *= 0.0025). An ARMS predicts psychosis onset within one year with good sensitivity (86%), specificity (91%), positive predictive value (80%) and negative predictive value (94%) [9,25].

3. Drug and alcohol use are assessed with the Composite International Diagnostic Interview (CIDI) [27]. The CIDI is a comprehensive, fully standardized instrument for assessing mental disorders according to the definitions and criteria of ICD-10 and DSM-IV. Good reliability and validity of the CIDI have been reported with all Kappa coefficients above .5 for reliability and above .7 for validity [28].

4. Semantic verbal fluency is assessed with a subtest of the Groninger Intelligence Test, a test that is part of a Dutch set of intelligence tests comparable to the Wechsler [29]. Participants have to name as many animals as possible in one minute. Schizophrenia patients do have more difficulties with tests like this compared to depressed patients and healthy controls, due to cognitive problems [30] F(2,63) = 3.8 *p *< .05. A poor result on this test could be a predictor for schizophrenia [31].

5. Depression is assessed with the Dutch translation of the Beck Depression Inventory second edition (BDI-II-NL) [32]. The BDI is a 21-item self-report questionnaire, which assesses the presence and severity of depressive symptoms. The score ranges from 0 - 63; a high score reflects more severe depression. The BDI-II is positively correlated to the Hamilton Depression Scale (Pearson r = .71). Also the test-retest reliability and the internal consistency show high rates (Pearson r = .93 and α = .91 respectively)

6. The Calgary Depression Scale (CDS) [33] is an 8-item interview that assesses depressive symptoms independent of the negative symptoms of schizophrenia with a goodness-of-fit index of 0.89 and a root square residual of 0.07. The internal reliability was good (α 0.85). The CDS shows weak statistically significant associations with the negative symptoms on the PANSS (0.33)

7. The Social Interaction Anxiety Scale (SIAS) [34] is a 20-item self-report questionnaire for social anxiety. Total scores range from 0 to 80. A high score on the SIAS reflects more severe social phobia. The SIAS discriminates significantly (*p *< .001) between social anxiety and other anxieties and healthy controls. High internal reliability (α ranges from .88 - .94) and test-retest reliability (α = .92) is reported for all scales.

8. Ethnic identity is assessed with the Dutch version of the ICSEY (International Comparative Study of Ethno Cultural Youth) Scale of Ethnic and National Identity [35,36]. This is a 10-item self-report questionnaire, which assesses ethnic and national affirmation, sense of belonging and feelings about being a group member. Each item is rated on a 5-point scale, ranging from 'strongly disagree' (1) to 'strongly agree' (5). No information about reliability and validity is reported.

9. The Personal Beliefs about Illness Questionnaire-Revised (PBIQ-R) [37] assesses the subjective appraisal of the illness. It is a self-report questionnaire with five subscales: 1) loss, 2) humiliation, 3) shame, 4) attribution of behaviour to self or to illness and 5) entrapment in psychosis.

10. The Euroqol-5D [38] assesses quality of life. It is a self-report questionnaire and measures general health-related quality of life. The list contains five dimensions (mobility, self-care, usual activities, pain and anxiety/depression). Each item score ranges from no to extreme problem level. Good reliability and validity are reported for use within a schizophrenic population [38].

11. Manchester Short Assessment of Quality of Life (MANSA) [39]. The MANSA was developed as a slightly modified instrument for assessing quality of life and satisfaction with specific life domains. The self-report questionnaire contains 16 items, which are rated on a 6-point scale. High face and construct validity was reported for assessing quality of life (coefficients above .82 for all domains). The measured quality of life isn't specifically illness or symptom related and therefore could be used for persons with several mental illnesses [39].

12. Genetic material will be derived from blood or saliva.

13. The Positive And Negative Syndrome Scale (PANSS) [40] is a 30 item structured interview that was developed for the assessment of positive (7 items) and negative (7 items) symptoms as well as general psychopathology (16 items) over the past two weeks. The PANSS uses 7-point Likert type scales. A study with 101 Schizophrenia patients [33] found the three scales to be normally distributed and found evidence of reliability and stability for the positive and negative scales (α .73 and .83, *p *< .001). The general psychopathology scale has a high internal consistency (α .79, *p *< .001)

14. The Psychosis Rating Scale (PSYRATS) [41]consists of two subscales that assess auditory hallucinations (11 items) and delusions (6 items). Inter-rater reliability is good, with coefficients in the range of .79 to 1.00. Validity was checked by comparing the PSYRATS with the Psychiatric Assessment (KGV) scale and the PANSS. Significant relationships were found for hallucinations and delusional disruption reported at the KGV, PANSS and PSYRATS [41].

15. The Dutch version of the Schedules for Clinical Assessment in Neuropsychiatry (SCAN 2.1) [42] will be used to assess the DSM-IV disorder status at baseline and when a transition to psychosis occurs. The SCAN 2.1 is a semi-structured, diagnostic interview for DSM-IV and ICD-10 designed by the World Health organization and translated into Dutch by Giel and Nienhuis [42]. This interview assesses all kind of symptoms belonging to the most common Axis I disorders, like mood disorders, anxiety disorders, eating disorders, psychotic disorders and cognitive decline. The reliability of this instrument is qualified as moderate to substantial. Diagnosis and non-diagnosis were recognised with a sensitivity of 86% percent and a specificity of 99%. Test-retest reliability was significant for diagnosis (k = .64).

16. Social Demographic Questionnaire (SDQ):

The sociodemographic questionnaire is developed by the researchers to assess socio-demographic factors in our study that may play a role in the development of a psychosis based on previous research and know risk factors for schizophrenia. The items are grouped by type:

**1. General: **e.g. Current residence; Birth; Relationship status; Household; Previous residences.

**2. Education: **e.g. number of years full-time; training completed; duplication number; highest level achieved; highest level completed; total numbers of education years; special education; cito-score.

**3. Current situation: **e.g. currently education; Number of months been successful in training last year; Paid job; Number of months been working successfully last year.

**4. DSM-IV: **e.g. have you ever received a psychiatric diagnosis? If yes, what diagnosis?

**5. Medication: **e.g. have you ever received medication? If yes, what medications?

**6. Bullying: **e.g. Have you been bullied in the past; at what age it started and stopped; Seriousness of harassment?

**7. Family data (Hetero-history): **e.g. General; Educational history of family.

**8. Family history: **e.g. familial psychiatric disorders; what degree of family.

**9. Pregnancy: **e.g. drugs, alcohol, smoking, anaemia during pregnancy; unwanted pregnancy; duration; age of mother at birth; APGAR-score; Birth weight; breastfeeding in baby time.

**10. Head injury: **e.g. involving injuries?

